### 8.1.2 *Multiple Ascending Dose (MAD)*

Part II of the study will explore multiple ascending dosing of *L. reuteri* expressing CXCL12 (activated ILP100-DP) in 3 sequential cohorts, each of 8 subjects. For each subject in a cohort, activated ILP100-DP, placebo and saline (NaCl) will be randomized to in total 8 wounds, 4 on the right arm and 4 on the left, in a 4:2:2 ratio (i.e. 4 wounds will be treated with activated ILP100-DP, 2 wounds will be treated with placebo and 2 wounds will be treated with saline as randomized). Activated ILP100-DP will be randomized to one of the arms and placebo and saline to the other arm. The IMPs will be administered on Day 1, Day 2 and Day 3 and then 3 times a week over the course of 3 weeks (in total 10 doses).

The proposed dose levels are  $5 \times 10^5$ ,  $5 \times 10^7$  and  $1 \times 10^9$  CFU/cm^2 wound area. The rationale for the starting dose and the planned dose escalation is detailed in Section 8.3. The doses, dose escalations and the dosing schedule may be adjusted based on emerging knowledge of safety and tolerability data observed in the SAD part of the study.

Subjects will come for 13 visits to the research clinic for screening, treatment and initial follow-up (Visit 1 to Visit 13), see Table 8.1-2 for details. After Visit 13, a 5-year long-term follow-up period (Visit 14 to 21) will be initiated as detailed below.

#### **Treatment phase (Visit 1 to Visit 13)**

Screening (Visit 1) will take place from Day -28 to Day -1. At Visit 2, eligible subjects will be admitted to the research clinic on Day 1 for pre-dose safety assessments and full-thickness wound punching with a biopsy punch (6 mm in diameter) on the ventral aspect of the upper arms (4 wounds/arm). The wounds should be separated by approximately 4 cm. Each wound will be numbered using a permanent marker (repeated at all post-dose visits). Prior to wound punching, subjects will be treated with local anesthesia (injected and/or topical) and the area will be cleaned with antiseptics (70% ethanol). The wound punching procedure will be detailed in a separate manual.

Subsequent to wound punching, the first dose of the IMP (activated ILP100-DP, placebo and saline) will be topically applied to each of the wounds in accordance with the randomization list. There should be 1 hour ( $\pm 10\%$ ) between the last wound punch and the start of IMP application to allow for pre-dose study assessments and hemostasis. Two unblinded persons will take part of the administration process, one will perform the application of IMP and the other one will confirm that the correct treatment is administered to the intended wound, i.e. in accordance with the randomization list. The IMP administration will be documented by video recording. Each wound will be dressed separately using an adhesive, transparent film, isolating the wounds from each other. An elastic, tubular bandage will be used on top of the films. Following IMP administration on Day 1 and Day 2, the wounds will be covered with adhesive, transparent film around the clock for 2 days and 2 nights (except during wound evaluations and IMP application). From Day 3 and onwards, the wounds will be treated with IMP and covered with adhesive, transparent film for 1 hour after IMP application where after the film will be removed. The wounds will be allowed to air dry and will then be separately covered with a non-occlusive dressing that can be used during showering and protects against contamination of viruses and bacteria. For details on the wound incision and IMP application processes, refer to Section 11.4 and Section 10.6, respectively.

The subjects will be carefully monitored by clinical staff during and after first dose and will remain at the research clinic for approximately 4 hours after dose. Vital signs and ECG will

be checked as detailed in Table 8.1-2. There is immediate access to equipment, qualified staff and an ICU in case of an acute emergency. Up to 4 subjects will be dosed on the same day.

The wounds will be photographed in a standardized setting according to instructions specified in a separate manual, and briefly summarized in Section 11.5, before treatment on Day 1, pre-treatment at the subsequent dosing visits, and at all follow-up visits to the research clinic. Selected members of the clinical staff will receive photography training prior to handling of the camera equipment. In addition, wounds will be analyzed using a 3D camera as outlined in Section 11.9.1.

Following the first dose on Day 1, subjects will come for 10 additional visits between Day 2 and Day 21 (Visits 3 to 12). The last dose will be given on Day 19 (Visit 11). Safety will be assessed by vital signs, safety laboratory parameters, local tolerability, AEs, use of concomitant medications and CXCL12 ADA analysis at visits outlined in Table 8.1-2.

The wounds must not at any visit be cleaned (unless necessary for safety reasons, e.g. due to an infection). The area surrounding the wounds should then be carefully cleaned with water if necessary. At visits when swabbing is performed, the area around the wound should be cleaned after swabbing if necessary. Before the subject leaves the research clinic, the wound should be dressed until healed.

Blood sampling for analysis of CXCL12 and *L. reuteri* systemic levels and a swab of the area surrounding the wounds and feces sampling for analysis of any presence of *L. reuteri* R2LC colonies containing the pSIP411 plasmid will be performed at time points and visits specified in Table 8.1-2.

For exploratory purposes, microcirculation assessments will be performed and dressings will be collected at time points outlined in Table 8.1-2.

An end-of-treatment phase visit (Visit 13) will take place on Day 32 ( $\pm 1$  day) or after early withdrawal.

### **Long-term follow-up (Visit 14 to Visit 21)**

After Visit 13, a 5-year long-term follow-up period (Visit 14 to 21) will be initiated. During the first year, subjects will visit the research clinic 6 weeks and 3, 6 and 12 months after treatment (Visit 14 to Visit 17). Following Visit 17, subjects will be followed-up yearly by visits to the research clinic.

Physical examination, AE and concomitant medication questioning, blood sampling for CXCL12 ADA analysis, photography (standard camera and 3D camera), local tolerability assessment (investigator), assessment of scar tissue formation, skin swab and feces sampling for analysis presence of *L. reuteri* will be performed at visits outlined in Table 8.1-2.

Subjects will be urged to contact the clinic in between visits, including long-term follow-up visits, in case of e.g. development of any new/recurrent cancer, development of infection, immunogenicity related reactions or local reactions associated with the wound/scar area. If considered relevant by the Investigator, extra visits will be scheduled.

### **General**

The investigator will assess local tolerability, wound healing and scar formation by direct observation. The subjects will assess local tolerability (pruritus and pain). Three to five independent experts will assess local tolerability, wound area, wound healing and scar

formation by using the wound/scar photographs. For details on timing of assessments, refer to Table 8.1-2.

Before initiating a new cohort, all subjects in the previous cohort must have been treated and 21 days safety and tolerability data for all treated subjects must have been evaluated by the iSRC, see Section 8.4.3. Once Day 21 safety and tolerability data for the last subject in each cohort has been collected, there will be at least 1 week between dose escalations.

Each subject is expected to participate for approximately 49 days (including a 28-day screening period) in the first phase of the MAD part and for an additional 5 years in the long-term follow-up.

The schedule of events is shown in Table 8.1-2. Study assessments are described in Section 11.

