| To determine the safety and tolerability of L. reuteri expressing CXCL12 (activated ILP100-DP) after topical single and multiple dose administration to experimentally induced skin wounds in healthy subjects | Occurrence and frequency of adverse events (AEs)                                                                                                                                                                                                                                                                   | SAD+
MAD | Investigator                                                                  | AE reporting and questioning (Section 11.7.1)                                                                                                                                                              |
|                                                                                                                                                                                                                       | Clinically significant changes in laboratory parameters, vital signs, ECG and physical examination findings                                                                                                                                                                                                        | SAD+
MAD | Investigator                                                                  | Blood sampling for clinical chemistry and hematology (Section 11.7.5),

Blood pressure and pulse (Section 11.7.3),

12-lead ECG (Section 11.7.4),

Physical examination (Section 11.7.2) |
|                                                                                                                                                                                                                       | Incidence of local reactions (each wound, 0-3)
○ Appearance of wound and wound edge (inflammation)
○ Condition of skin surrounding the wound (inflammation)
○ Hemorrhage
○ Amount of exudate present
○ Presence of slough/necrotic tissue
○ Presence of granulation tissue
○ Hypergranulation | SAD+
MAD | Investigator (direct observation)

Independent evaluators (photography) | Local tolerability (Section 11.7.6.1)

Photography (Section 11.5)                                                                                                                                    |

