### **General**

Over the course of the study, the investigator will assess local tolerability, wound healing and scar tissue formation by direct observation. The subjects will assess local tolerability (pruritus and pain). Three to five independent experts will assess local tolerability, wound area, wound healing and scar tissue formation by using the wound/scar photographs. For details on timing of assessments, refer to Table 8.1-1.

Before initiating a new cohort, all subjects in the previous cohort must have been treated and Day 3 safety and tolerability data for all treated subjects must have been evaluated by the iSRC, see Section 8.4.3. Once Day 3 safety and tolerability data for the last subject in each cohort has been collected, there will be at least 1 week between dose escalations.

Each subject is expected to participate for approximately 42 days (including a 28-day screening period) in the first phase of the SAD part and for an additional 5 years in the long-term follow-up.

The schedule of events is shown in Table 8.1-1. Study assessments are described in Section 11.

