| Body temperature                               |                 | X             |                                                               |       |                                                         |                   |                                     |                                               |                      |                      |                       |                          |                      |
| Hematology, coagulation and clinical chemistry | X               | X             | X                                                             |       |                                                         |                   | X                                   |                                               |                      |                      |                       |                          |                      |

| Visit number                                                | Treatment phase |                           |                                                               |                     |                                                         |                   |                                     | Long-term follow-up                           |                      |                      |                       |                          |                      |
|-------------------------------------------------------------|-----------------|---------------------------|---------------------------------------------------------------|---------------------|---------------------------------------------------------|-------------------|-------------------------------------|-----------------------------------------------|----------------------|----------------------|-----------------------|--------------------------|----------------------|
|                                                             | Year 1          |                           |                                                               |                     |                                                         |                   |                                     |                                               |                      |                      | Year 2-4              | Year 5                   |                      |

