| CXCL12 ADA sample                                           |                 | X             |                                                               |                     |                                                         | X                 |                                     | X                                             |                      |                      | X                     | X                        | X                    |
| Wound incision by punch biopsy                              |                 | X                         |                                                               |                     |                                                         |                   |                                     |                                               |                      |                      |                       |                          |                      |
| IMP administration                                          |                 | X                         | X                                                             | X                   | X                                                       |                   |                                     |                                               |                      |                      |                       |                          |                      |
| IMP for viable count                                        |                 | X            |                                                               |                     | X                                          |                   |                                     |                                               |                      |                      |                       |                          |                      |
| Wound/scar photography                                      |                 | X            | X                                                             | X                   | X                                                       | X                 | X                                   | X                                             | X                    | X                    | X                     |                          |                      |

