#### 8.4.3 *Internal safety review committee*

Before initiating a new cohort, all subjects in the previous cohort must have been treated and 3 days (SAD) and 21 days (MAD) safety and tolerability data for all treated subjects must have been evaluated by the iSRC. Based on emerging safety and tolerability data, the amount of required safety data to be reviewed after a completed cohort might be adjusted. Details regarding timing of iSRC review and the data to be reviewed and the documentation procedure will be provided in a separate iSRC charter.

The voting members of the iSRC will consist of the Principal Investigator, the Medical Monitor (i.e. the Sponsor's medically responsible person) or delegate and an independent, external clinical expert. The clinical research manager (CRM), and additional Sponsor representatives will be invited as appropriate. Further internal or external experts may be consulted by the iSRC as necessary.

An adaptive dosing strategy will be applied to allow for a flexible and safe dose escalation. The planned dose escalation is outlined in Section 8.3.1. The actual doses given in each cohort will be guided by the iSRC recommendations based on available safety and tolerability data. Every dose step is thus adjustable and the recommendation to the Sponsor may be to continue with a higher or lower dose than the intended dose, repeat the same dose level, continue with an intermediate dose level or to stop dosing.

The decision of the iSRC on the recommendation of the next dose level will be taken in consensus between the iSRC members and documented as appropriate. In case there is disagreement between the 3 voting members, the most conservative approach will be taken. It is not acceptable to repeat a dose level where any of the dose escalation stopping rules have been met.

The treatment code for individual wounds may be broken by the iSRC during the assessment process (partial un-blinding) in accordance with stopping criteria described in Table 8.4-1. The medical staff and the subjects will still be blinded for the treatments (active drug, placebo or saline) to be administered in the subsequent dose groups/cohorts in order to minimize bias. If unblinding was considered necessary, the iSRC meeting may consist of a closed part and an open part.

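### MAD part: no safety laboratory panel between Day 2 and Day 32, so escalation can proceed with no required labs after doses 3 to 10

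*Protocol*

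**What the plan says.** **Review before escalation.** For the MAD part, Section 8.1.2 (General) requires that "21 days safety and tolerability data for all treated subjects must have been evaluated by the iSRC". After the last subject's Day 21 data are collected, "there will be at least 1 week between dose escalations". Section 8.4.3 repeats the requirement for both parts: "3 days (SAD) and 21 days (MAD) safety and tolerability data for all treated subjects must have been evaluated by the iSRC".

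**Laboratory schedule.** Section 8.1.2 names safety laboratory parameters as a safety assessment and refers their timing to Table 8.1-2. In that table the row "Hematology, coagulation and clinical chemistry" is marked at screening, Day 1 (before wound punching), Day 2 and Day 32 (±1 day). The cells for Day 3, Days 5 to 19 and Day 21 are blank. Urine dip stick is marked at screening, Day 1 and Day 32. Section 11.7.5 lists the parameters and adds no time points.

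**Dosing.** There are ten doses: Days 1, 2, 3, 5, 8, 10, 12, 15, 17 and 19.

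**Endpoint.** Section 7.1.1 includes among the primary endpoints: "Clinically significant changes in laboratory parameters, vital signs, ECG and physical examination findings".

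**The concern.** The MAD part exists to find out whether repeated dosing is safe. The committee that allows each dose increase should therefore see laboratory results obtained after repeated dosing. As scheduled, the latest required panel is from Day 2, after one or two doses, and the next is not due until after escalation is already permitted.

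Two things could follow. A silent laboratory change that arises after Day 2 and resolves by Day 32 would not be seen by any scheduled panel. One that persists would be measured only after subjects in the next cohort may have begun dosing. The stopping rules in Table 8.4-1 do not close this gap. They act on related SAEs and severe AEs, and an asymptomatic laboratory abnormality can become an AE only if a sample is taken.

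The SAD part has no such gap. There the rule is "Day 3 safety and tolerability data for all treated subjects must have been evaluated by the iSRC", and the Day 2 panel follows the only dose and precedes that review. The MAD row has the same pattern (screening, Day 1, Day 2, end-of-treatment visit), although it now spans ten doses.

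**Working it through.** The protocol performs no sample size calculation, so there is no power figure to reproduce. The check uses the visit schedule.

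**1. Number of doses.** The dosing days in Table 8.1-2 are 1, 2, 3, 5, 8, 10, 12, 15, 17 and 19. That is 10, which matches the stated total.

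**2. Position of the laboratory marks.** Two rows were mapped to the same column headers:

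| Row | Screening | Day 1 | Day 2 | Day 3 | Days 5–19 | Day 21 | Day 32 |
|---|---|---|---|---|---|---|---|
| Hematology, coagulation, chemistry | X | X | X | – | – | – | X |
| Vital signs | X | X | – | X | X | X | X |

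The vital-signs row fills the on-treatment columns as expected, so the blanks in the laboratory row are not a column shift.

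**3. Doses with no panel before the decision.** Doses after Day 2 fall on Days 3, 5, 8, 10, 12, 15, 17 and 19, which is 8 of 10. The table does not say whether the Day 2 sample is drawn before dose 2. If it is, the count is 9 of 10.

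**4. Intervals.**
- Between panels: 32 − 2 = 30 days. With the Day 32 window: 31 − 2 = 29 to 33 − 2 = 31.
- Last dose to next panel: 32 − 19 = 13 days. With both windows (Day 19 ±1, Day 32 ±1): 31 − 20 = 11 to 33 − 18 = 15.

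**5. Earliest permitted escalation, counted in the last subject's days.** 21 + 7 = Day 28. With Day 21 ±1: Day 27 to Day 29.

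**6. Shortfall to the Day 32 panel.** 32 − 28 = 4 days. Minimum 31 − 29 = 2; maximum 33 − 27 = 6. The one-week wait never brings the last subject's Day 32 panel into the review.

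**7. Exposure in the next cohort by then.** If its first subject starts on Day 28, Day 32 is that subject's Day 5 (range Day 3 to Day 7). Doses on Days 1, 2, 3 and 5 make 4 of 10, or 3 if it is only Day 3. The dose steps are 5×10⁷ / 5×10⁵ = 100-fold (cohort 1 to 2) and 1×10⁹ / 5×10⁷ = 20-fold (cohort 2 to 3).

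**8. Blood volume if one panel is added.** Section 12.2 caps the MAD part at 200 mL. Plasma CXCL12: 10 samples × about 5 mL = 50 mL (Table 8.1-2 footnotes, Section 11.8.1). The document does not give the other volumes, so they are assumed: ADA 8 × 5 = 40 mL; screening serology 5 to 10 mL; four safety panels at 10 to 15 mL = 40 to 60 mL. The total is 135 to 160 mL, or 145 to 175 mL with a fifth panel, below the cap.

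**The case against.** The table reading and the dates are not disputable. The case against concerns weight, and several parts of it are fair.

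- **Other samples are taken.** ADA is drawn on Day 21. Plasma CXCL12 is sampled up to Day 21, and blood is cultured for the product on Days 3, 5, 8, 15 and 21. Vital signs, a Day 10 ECG, local tolerability and AEs are also collected. This stands, so the gap is specifically in hematology, coagulation and chemistry, with urinalysis. None of the other measures substitutes for that panel.
- **Low prior risk.** Systemic exposure is predicted to be very low or undetectable. Minipigs received 15 applications over 4 weeks, at 260 times the top MAD dose per body surface area, with no clinical chemistry differences. Film is kept on around the clock only after the Day 1 and Day 2 doses, and from Day 3 it comes off after an hour. Both upper MAD levels are planned SAD levels with Day 2 and Day 14 panels. This lowers the expected risk, but SAD labs follow one dose to two wounds, whereas the MAD part gives ten doses to four.
- **Worst-case timing.** A subject who started at least 4 days before the last one (32 − 28) would nominally have a Day 32 panel by the earliest escalation. That is true, but its review is not required. Up to four subjects may be dosed per day, so a cohort of eight could start on two consecutive days, and then nobody would have reached Day 32.
- **Discretion and the charter.** Section 8.4.3 leaves review details to an iSRC charter that is not shown. Section 8.4 lets sampling times be adjusted, and Section 6.3 allows extra visits. The charter could already require waiting for Day 32. However, the sampling adjustments and extra visits are permissions that depend on results or emerging data, and a silent laboratory change gives no prompt. The protocol itself fixes both the sampling days and the minimum review data.
- **Rolling review.** It could act on a persistent Day 32 abnormality, but only after the next cohort may have been exposed.

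**Conclusion.** The concern holds and should be fixed. Followed exactly as written, the protocol permits each of the two planned MAD escalations with no required hematology, coagulation or chemistry result after doses 3 to 10: 8 of 10 doses, or 9 of 10 if the Day 2 sample is pre-dose. The next panel comes nominally 13 days after the last dose and 4 days (2 to 6) after escalation is first allowed.

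The count of required results depends only on the table and the review rule. The figure of 3 to 4 doses already given in the next cohort assumes that cohort starts on the first permitted day and is measured against the last subject of the previous one. No actual harm is claimed, and the expected risk with this topical product is low. The weakness is that the escalation decision lacks required data on a primary endpoint under the regimen being tested.

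**What to change.** Do one of the following.

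1. **Add a Day 21 panel (preferred).** Mark Visit 12 (Day 21) in the "Hematology, coagulation and clinical chemistry" row of Table 8.1-2. Blood is already drawn at that visit, for example for the "CXCL12 ADA sample". The result comes 2 days after the last dose (21 − 19) and becomes part of the 21-day data. The cost is one table mark and one more panel of blood, with no extra visit; under the volume assumptions above, the total stays within the 200 mL limit.
2. **Keep the schedule and wait.** State in Sections 8.1.2 and 8.4.3 that the Visit 13 (Day 32) panel of all treated subjects belongs to the minimum iSRC data before each MAD escalation. The cost is nominally 4 days (2 to 6) plus laboratory turnaround, for each of two planned escalations.
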